### Randomisation

Participants were assigned to the programme or the no-treatment control group directly after the baseline measurement using stratified randomisation. This randomisation was performed in blocks of two on the basis of one prognostic factor: the level of concern about falls (some, regular, often, and very often). Computerised alternative allocation was used in the randomisation process, which was performed by an external agency.

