### Outcomes

#### Effect evaluation

Table 2 presents the outcomes of the effect evaluation.

**Table 2 T2:** Outcome measures of the effect evaluation

Primary outcome measures	Instrument	No. of items	Range*	S	B	FU1	FU2
concerns about falls	FES-I [33,34,53]	16	16 to 64	-	TI	TI	TI
avoidance of activity owing to concerns about falls	FES-IAB	16	16 to 64	-	TI	TI	TI

**Secondary outcome measures**	**Instrument**	**No. of items**	**Range***	**S**	**B**	**FU1**	**FU2**

activities of daily life	GARS [35]	18	18 to 72	-	TI	TI	TI
no. of falls	N/A	1	N/A	-	C >	C >	C >
- indoor	N/A	1	N/A	-	C >	C >	C >
- outdoor	N/A	1	N/A	-	C >	C >	C >
no. of times medical attention required as a result of falls	N/A	1	N/A	-	C >	C >	C >

**Tertiary outcome measures**	**Instrument**	**No. of items**	**Range***	**S**	**B**	**FU1**	**FU2**

perceived consequences of falling - loss of functional independence subscale	CoF [9]	6	6 to 24	-	TI	TI	TI
perceived consequences of falling - damage to identity subscale	CoF [9]	6	6 to 24	-	TI	TI	TI
catastrophic beliefs about consequences of a fall	CAFS [37]	5	5 to 20	-	TI	TI	TI
perceived control over falling	PCOF [38]	4	4 to 16	-	TI	TI	TI
mastery	Personal Mastery Scale [39]	7	7 to 35	-	TI	TI	TI
feelings of anxiety	HADS-A [40,41]	7	0 to 21	-	TI	TI	TI
symptoms of depression	HADS-D [40,41]	7	0 to 21	-	TI	TI	TI
social support interactions	SSL 12-I [42]	12	12 to 48	-	TI	TI	TI
health-related quality of life	SF-12 [43]	12	12 to 36	-	TI	TI	TI

**Additional variables**	**Instrument**	**No. of items**	**Range***	**S**	**B**	**FU1**	**FU2**

demographic data (age, gender, living situation, educational level)	N/A	5	N/A	SQ	-	-	-
perceived general health	Perceived general health [23]	1	1 to 5	SQ	-	-	-
cognitive impairment	AMT4 [24]	4	N/A	-	TI	-	-
	TICS [25]	11	0 to 41	-	TI^#^	-	-
chronic medical conditions	Chronic medical conditions questionnaire [46]	5	0 to 5	-	TI	-	-
concerns about falls	N/A	1	1 to 6	SQ	TI	TI	TI
avoidance of activity owing to concerns about falls	N/A	1	1 to 6	SQ	TI	TI	TI
no. of falls in the previous 6 months	N/A	1	1 to 6	SQ	TI	-	-
no. of falls in the previous 5 months	N/A	1	1 to 6	-	-	TI	-
no. of falls in the previous 7 months	N/A	1	1 to 6	-	-	-	TI
expectations of intervention	Adapted expectations questionnaire [47]	4	4 to 20	-	TI	-	-

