### Sample size and power

Sample size calculations are based on outcomes of a previous study using the Falls Efficacy Scale-International (FES-I) among older people in The Netherlands [53]. Two times 112 participants will provide 80% power at alpha 0.05 (one-tailed) to detect differences between the intervention and control groups' mean score of at least 3.8 points (SD is 11.4 equivalent with an effect size of 0.33 on the FES-I). However, a dropout rate of 20% during the study is expected, based on the experiences in the home visit study from Van Haastregt et al. [54]. Therefore, 2 × 140 participants are needed to enrol in the trial.

In a previous Dutch study, 54% of the population reported fear of falling, 38% reported related avoidance behaviour, and 48% reported poor or fair perceived general health [8]. Based on the experiences in that study and on the evaluation of AMB-NL [15], we estimate that approximately 6% of the older people who return the screening questionnaire will meet all inclusion and exclusion criteria and will be interested in participating in the trial. With an estimated response rate of 55%, a minimum sample of 8,200 older persons aged 70 or over needs to be approached with a screening questionnaire.

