### Analysis

Descriptive techniques will be used to describe the study groups. Baseline variables will be compared, to detect differences between the participants of both groups at the start of the study. Data of the effect evaluation will be analysed according to both the intention-to-treat and per-protocol principles. In the first analyses all participants will be included according to their original assignment [52]. Participants of the intervention group who attended at least five of the seven programme sessions will be included in the per-protocol analysis. Based on prior work, five sessions of the programme are considered as sufficient programme exposure [15,18]. Mixed-effects regression analyses will be applied, to test for between-group differences with respect to the primary, secondary and tertiary outcome measures at all follow-up assessments. Models will be adjusted for the following covariates, considered as relevant for the outcomes [8]: concerns about falls, age, gender, perceived general health, and number of falls in the past 6 months at baseline. Additional covariates will be included in the analysis if baseline differences are detected for variables relevant for the outcomes. The level of statistical significance will be set at 0.05 (one-tailed). Data on the process and economic evaluation will be analysed and presented using descriptive techniques and appropriate statistical testing.

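### The single covariate list does not secure adjustment for the outcome's own baseline on FES-IAB, GARS or the tertiary scales, and does not say which concern measure it means

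*Protocol article*

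**What the plan says.** The Analysis section plans mixed-effects regression for the primary, secondary and tertiary outcomes, comparing groups at each follow-up. It gives one adjustment set for all of them: "concerns about falls, age, gender, perceived general health, and number of falls in the past 6 months at baseline". Any other baseline variable is added only when the groups are found to differ on it and it is relevant to the outcome.

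Table 2 (Outcomes, Effect evaluation) lists two primary outcomes. The second, "avoidance of activity owing to concerns about falls", is measured by the 16-item FES-IAB at baseline, 5 months and 12 months. GARS and every tertiary scale have the same three assessments.

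Table 2 also carries concern about falls twice: as FES-I (16 items, range 16 to 64) and as a one-item question (range 1 to 6) asked at screening, baseline and both follow-ups. The Randomisation section stratifies on "the level of concern about falls (some, regular, often, and very often", without naming the instrument.

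The sample-size section works from FES-I only, one-tailed at 0.05, for a difference in "mean score of at least 3.8 points", where the "SD is 11.4 equivalent with an effect size of 0.33 on the FES-I". It mentions no reduction in variance from baseline adjustment.

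**The concern.** A scale's own baseline is usually its strongest single predictor. The list treats outcomes unevenly. Fall counts have a baseline equivalent (falls in the past 6 months). FES-I may have one, depending on what the first covariate means. FES-IAB, GARS and the tertiary scales have none by name.

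The rule for extra covariates makes own-baseline adjustment depend on a look at the data. An imbalance too small to be detected stays out of the model, and the precision that the baseline would give is not obtained when the groups look alike.

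The ambiguity adds to this. If the listed covariate is the one-item question, the FES-I model lacks baseline FES-I. If it is baseline FES-I, the stratification factor is in no model. Neither reading secures both.

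**Working it through.** **1. The plan's own figure.** Inputs from the sample-size section: difference 3.8, SD 11.4, one-sided 0.05, power 80%.

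n per group = 2 × (1.645 + 0.842)² × (11.4/3.8)² = 2 × 6.18 × 9 ≈ 111.3, so 112. Allowing for 20% dropout, 112/0.8 = 140. Both stated figures reproduce with the unadjusted SD, so the plan takes no credit for baseline adjustment. With 389 enrolled, 389 × 0.8 ≈ 311 would be analysed, about 156 per group. Unadjusted one-sided power for FES-I is then about 90%.

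**2. Gain from adding baseline FES-IAB to baseline FES-I.** The documents give no correlations, so all of these are assumed. Let r1 be the correlation of baseline with follow-up FES-IAB, r2 that of baseline FES-I with follow-up FES-IAB, and r12 that between the two baselines.

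- Residual variance with FES-I only: 1 − r2².
- With both: 1 − (r1² + r2² − 2·r1·r2·r12)/(1 − r12²).

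| r1 / r2 / r12 | FES-I only | both | reduction | ratio |
|---|---|---|---|---|
| 0.6 / 0.4 / 0.7 | 0.84 | 1 − 0.184/0.51 = 0.64 | 24% | 1.31 |
| 0.6 / 0.5 / 0.85 | 0.75 | 1 − 0.100/0.2775 = 0.64 | 15% | 1.17 |

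The ratio is the equivalent gain in participants: 31% and 17%. The second row is plausible because an avoidance item is asked only when the person has at least some concern about that activity, which ties FES-IAB to FES-I.

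**3. A wider range for other scales.** Assume that baseline concern predicts follow-up only through the outcome's own baseline, correlates a with that baseline, and that the baseline correlates ρ with follow-up. The ratio of required n with and without the own baseline is (1 − ρ²)/(1 − a²ρ²).

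- ρ = 0.5, a = 0.85: 0.75/0.819 = 0.92, about 8% fewer.
- ρ = 0.8, a = 0.3: 0.36/0.942 = 0.38, about 62% fewer.

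**4. FES-I, if the covariate is the one-item question.** Against no baseline adjustment, an own-baseline correlation of 0.5 to 0.7 gives a variance factor 1 − r² of 0.75 to 0.51, a reduction of 25% to 49%. The forgone gain is smaller than this by whatever the one-item question recovers.

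**5. Imbalance that escapes detection.** With about 194 per group, the standard error of a baseline difference is √(2/194) ≈ 0.10 SD. The article does not define detection. If it means a conventional two-sided 5% test, an imbalance of nearly 0.2 SD can pass. With no adjustment and r1 = 0.6, this shifts the estimate by 0.6 × 0.2 = 0.12 SD. With baseline FES-I in the model, and FES-I imbalanced to the degree its correlation implies, the shift is (r1 − r2·r12) × 0.2. That is 0.32 × 0.2 ≈ 0.06 SD for the first row of the table and 0.175 × 0.2 ≈ 0.04 SD for the second.

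**The case against.** The strongest reply is that the article specifies a mixed model for outcomes measured at baseline, 5 and 12 months. If baseline is one of the responses, own-baseline information is used without appearing in a covariate list. The article does not exclude this, and a journal article may leave such detail to the full protocol. This stands, and it makes the loss conditional. A baseline concern covariate together with testing at the follow-up assessments makes follow-up-only responses the more natural reading, but does not settle it.

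A reader might infer more than the documents support:

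- **That precision is lost as a fact, by a known amount.** The model may recover it, and the correlations are assumed. The calculation also ignores the other listed covariates, which may already explain part of an outcome such as GARS.
- **That chance imbalance passes straight into the estimate.** A detected imbalance in a relevant variable would trigger adjustment, and the listed covariates absorb part of the rest. What remains is undetected imbalance, partly corrected. Under randomisation, leaving out a prognostic covariate does not bias the linear-model comparison on average.
- **That the trial is underpowered.** The 112 and 140 per group rest on the unadjusted SD, and enrolment exceeded the plan.
- **That omitting the stratum makes the tests too liberal.** Omitting a prognostic stratification factor generally leaves the standard error too large, which is conservative, and baseline FES-I would probably absorb much of the effect. That the one-item question supplies the strata is plausible but not stated.

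None of this answers the textual point. The list and its rule for additions are stated explicitly, and as stated they do not guarantee own-baseline adjustment for a primary outcome.

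**Conclusion.** The point holds in conditional form. As written, the plan does not secure own-baseline adjustment for FES-IAB, GARS or the tertiary scales, makes it depend on detected differences, and does not identify the concern covariate. FES-IAB matters most because it is a primary outcome.

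The 15% to 24% reduction for FES-IAB assumes that baseline FES-I is already in the model and that baseline does not enter another way. If FES-I is indeed the listed covariate, the FES-I analysis itself loses nothing. At stake are efficiency and a rule fixed in advance, not the validity of the comparison or the planned sample size. It is worth changing because the change is almost free.

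**What to change.** Before any group comparison is seen, reword the covariate rule:

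- Every continuous outcome model includes the baseline value of that same outcome (or baseline as a response constrained equal across groups) and the four-level randomisation stratum, plus age, gender, perceived general health and falls in the past 6 months.
- These terms are included whatever baseline differences are observed.
- The instrument meant by concerns about falls is named, and so is the instrument that defines the stratum.
- The FES-I model includes both baseline FES-I and the stratum.
- For fall counts, falls in the past 6 months remain the baseline value.

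All these values are already collected, so the cost is wording. The added terms take up to about four degrees of freedom (three for the stratum, one for the baseline), trivial with about 311 analysed. The sample size need not change.

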## Background

Falls and concerns related to falls are very common in community-dwelling older people. About one in three older people living in the community experiences at least one fall each year, of which roughly half results in an injury [1,2]. Interestingly, around two-thirds of older people report concerns related to falls [3], of which roughly half report activity avoidance as a result of these concerns [4-8]. Concerns about falls can be present in both people who have fallen and people who have not [9]. These concerns have been linked to decreased balance performance, decreased mobility, functional decline, low quality of life, institutionalisation and falls [3,10-13]. Recent research has shown that concerns about falls can lead to falls irrespective of any physiological fall risk [13].

Concerns about falls can be considered as a multifactorial problem [14,15]. As a consequence, successful programmes should not only target concerns about falls but should also focus on aspects like increasing self-efficacy and a sense of control regarding the risks of falling, setting realistic goals for increasing activity, changing the environment to reduce the fall risk and promoting physical activity to increase strength and balance [15-19].

Cognitive behavioural therapy could be seen as a suitable strategy to reduce concerns about falls by modifying patterns of thoughts (cognition) and actions (behaviour) that contribute to the concern.

One of the programmes with proven effectiveness is the Dutch version of 'A Matter of Balance' (AMB-NL) [20]. This multicomponent cognitive behavioural group programme consists of eight weekly group sessions and a booster session after six months. It has shown favourable effects on concerns about falls, perceived control over falling and daily activity, after at least 8 months of follow-up. In addition, significantly fewer recurrent fallers were observed in this group after 14 months of follow-up [15]. Notwithstanding these positive outcomes, approximately 40% of the participants attended less than five sessions out of a total eight, mainly because of health problems [21]. It seems that, in particular, frail older people refrained from attending the group programme. This is also seen in other group programmes that explicitly address concerns about falls, and target frail older people living in the community [18,22].

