### Recruitment of participants

Three communities, Maastricht, Sittard-Geleen, and Heerlen, situated in the southeast of The Netherlands have been selected for participation in the trial. The municipal registry offices selected 11,490 addresses of community-dwelling people of 70 years or over in their district, at random. To screen for eligibility, people received a short postal questionnaire with a freepost envelope, as well as information about the trial and an informed consent form. After a fortnight, reminder letters were sent. The questionnaire assessed socio-demographics and fall-related variables and inclusion and exclusion criteria.

Older people were included if they met all of the following criteria: 1) they reported at least some concerns about falls; 2) they reported at least some associated avoidance of activity; 3) they perceived their general health as fair or poor [23]; 4) they lived in the community; 5) they were 70 years of age or older; and 6) they were willing to participate (signed informed consent form). People were excluded if they were confined to bed, were restricted by the permanent use of a wheelchair, were waiting for a nursing home admission, experienced substantial hearing or vision impairments or they failed the shortened version of the Abbreviated Mental Test (AMT4) [24] assesses cognitive impairment and, subsequently, the Telephone Interview Cognitive Status (TICS) [25]. In addition, a restriction was applied to couples; to prevent reciprocal influencing only one partner of a couple was allowed to participate in the trial. Lots were drawn if this selection process was necessary.

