#### Additional variables

Several variables are assessed to provide insight into the population under study, and to interpret the outcomes of the study. The socio-demographic and health-related variables, assessed during the process of screening for eligibility, are: age, gender, living alone or not, educational level, perceived general health (item one of the MOS SF-20) [23,44], and self-reported impaired vision and hearing [45]. Other health-related variables assessed during the baseline measurement are: chronic medical conditions (a 5-item checklist) [46] and cognitive status (AMT4: shortened version of the Abbreviated Mental Test; 4 items and TICS: Telephone Interview Cognitive Status; 11 items) [24,25]. Furthermore, 1-item questions on concerns about falls, the avoidance of activities owing to these concerns and the number of falls are assessed at baseline, as well as at all follow-up measurements. Lastly, at the baseline, participants are asked about their outcome expectations with regard to the programme [47].

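### The fixed covariates carry general health only as a two-level item; baseline disability and chronic conditions, already collected, should be prespecified rather than left to a baseline-imbalance trigger (minor, free improvement)

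*Protocol article*

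**What the plan says.** **Covariates.** The protocol article (Analysis) plans mixed-effects regression for all outcomes at both follow-ups, adjusted for "concerns about falls, age, gender, perceived general health, and number of falls in the past 6 months at baseline". They were chosen for their relevance to the outcomes, with a citation. Others are admitted conditionally: "Additional covariates will be included in the analysis if baseline differences are detected for variables relevant for the outcomes".

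**The health item.** Table 2 lists perceived general health as one item, range 1 to 5, taken from the screening questionnaire only. Under Recruitment of participants, one entry criterion is that "they perceived their general health as fair or poor".

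**Health measures not in the fixed list.** Table 2 has the 18-item GARS, range 18 to 72, at baseline and both follow-ups. Additional variables lists "chronic medical conditions (a 5-item checklist"), range 0 to 5, at baseline. Under Randomisation, allocation follows the baseline measurement, so both are pre-randomisation values.

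**Dropout and attendance.** Sample size and power states that "a dropout rate of 20% during the study is expected", taken from an earlier home-visit study. The Background reports that in the parent group programme "approximately 40% of the participants attended less than five sessions out of a total eight, mainly because of health problems".

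**The concern.** Covariates earn their place in a randomised comparison by predicting the outcome, and in a mixed model also by predicting who is lost. Here the one general-health term has been narrowed by eligibility, while two fuller health measures stand outside the model. The rule that could bring them in looks at the wrong thing. A baseline difference between randomised arms is chance, and its size says nothing about how strongly the variable predicts FES-I or FES-IAB. Nor can a check on the full randomised sample see an imbalance that develops later among those still followed.

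Two things are at stake. The more certain is precision: prognostic information already paid for may go unused. The less certain is protection against selective loss. If frailer programme participants left follow-up more often than frailer controls, the retained programme arm would be healthier, and the comparison would drift in its favour.

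**Working it through.** **1. The plan's own figure.** Inputs (Sample size and power): difference 3.8, SD 11.4, one-tailed alpha 0.05, power 80%. n per group = 2 × (1.645 + 0.842)² × (11.4/3.8)² = 2 × 6.18 × 9 ≈ 111.3, so 112. With 20% dropout, 112/0.80 = 140. Both figures reproduce, and this point does not change them.

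**2. How much health information the item keeps.** Assume a normal latent health variable, 48% of people rated fair or poor (the share quoted in Sample size and power) and 5% to 20% rated poor (assumed).

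| Assumed correlation of item with true health | R², five levels, all people | R², two levels, eligible people | Health variance left among eligible |
|---|---|---|---|
| 0.5 | 0.22–0.23 | 0.05–0.07 | 84% |
| 0.7 | 0.42–0.44 | 0.13–0.17 | 68% |

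Most of the variation in health survives selection, but the item captures little of it.

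**3. How often the trigger would act.** The article does not say how a difference is detected. If it were a test at 0.05 (assumed), each variable would enter in 5% of trials however prognostic it was. At least one of the two would enter in 5% (fully correlated) to 1 − 0.95² = 9.75% (independent).

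**4. Precision and bias: null simulation.** 389 randomised, no true effect, 20% lost by 12 months (half before 5 months), SD 11.4. Assumed: a standardised slope of disability on follow-up FES-I, given baseline concern, of 0.15 or 0.30; a dropout odds ratio per SD of disability of 2.5 to 4 in the programme arm and 1 in controls. The comparator model holds baseline concern and a fair/poor indicator. Each cell was run with 800 replicates and again with 6,000.

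| Slope | Bias without disability (800; 6,000) | One-tailed type I error without disability | With disability |
|---|---|---|---|
| 0.15 | −0.08 to −0.25; −0.15 to −0.19 | 6.5–8.1%; 6.8–7.5% | 4.9–5.1%; 4.8–4.9% |
| 0.30 | −0.31 to −0.37; −0.30 to −0.41 | 9.9–10.2%; 8.4–10.8% | 5.6–6.4%; 5.0–5.3% |

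Hand check on the larger run, using the SDs of the estimate below: Φ(0.15/1.05 − 1.645) = Φ(−1.50) ≈ 6.7%, and Φ(0.41/0.98 − 1.645) = Φ(−1.23) ≈ 11%. These agree with the ends of the simulated range.

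SD of the estimate: 1.05 to 1.04 at slope 0.15 (0.01/1.05 ≈ 1%) and 0.98 to 0.93 at slope 0.30 (0.05/0.98 ≈ 5%). The larger run gives about 1% to 6%. In sample-size terms this is 1/0.99² − 1 ≈ 2% to 1/0.94² − 1 ≈ 13% more participants.

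**5. A separate model with a true effect of −3.8.** Single follow-up; all correlations and dropout slopes assumed.

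| Adjusted for | Frailty-related dropout equal in both arms (about 21%) | In programme arm only (20.9% v 18.3%) |
|---|---|---|
| Baseline concern | −3.83 | −4.23 |
| + two-level health item | −3.83 | −4.19 |
| + disability score | −3.83 | −3.96 |

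Unadjusted, the unequal case gives −4.68. The two-level item removes 4.23 − 4.19 = 0.04 points of bias, and disability a further 4.19 − 3.96 = 0.23, leaving 3.96 − 3.80 = 0.16. With equal dropout, no model is materially biased.

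**The case against.** The case against has force.

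- **Cause of dropout.** A reader might infer that the trial expects its dropout to be driven by health. The documents do not say so. The 20% is carried over from an earlier study with no cause given. The health statement in the Background concerns session attendance in a group programme, which the in-home format was designed to make easier. This objection stands.
- **Follow-up of non-compliers.** Under Data collection, programme participants who do not comply are still approached for every follow-up, and those with missing data are contacted. This weakens the link between stopping sessions and leaving follow-up, though the plan still allows for 20% loss. It stands in part.
- **Bias.** A reader might also infer that the planned estimate is biased towards the programme. That needs a strong health–dropout relation in one arm and none in the other, and nothing in the documents supports such a contrast or its direction. This stands.
- **The comparator model.** The simulation omits age, gender and previous falls, all of which the plan includes and which may carry health information. The residual bias of the planned model is therefore probably overstated.
- **Monte Carlo error.** With 800 replicates the standard error near 5% is √(0.05 × 0.95/800) ≈ 0.8 percentage points, so 6.5% alone would not be convincing. With 6,000 it is about 0.3 points, and the excess persists under the stated assumptions.
- **Judgement and omitted detail.** Five covariates named in advance is a defensible choice, and the cited source for them is not at hand. Missing-data handling and a comparison of retained with lost participants may sit in the full protocol or SAP, so their absence here is no finding.

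The objections do not rescue the conditional rule. The article states it explicitly, and it selects on chance imbalance rather than on prognostic value, the article's own criterion for the fixed list.

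**Conclusion.** The point holds as a minor, free improvement, not as an error in the plan. Eligibility confines the only general-health covariate to two of five levels, and two fuller baseline health measures can enter only through a trigger unrelated to their prognostic strength.

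The gain that does not depend on dropout is a standard error about 1% to 6% smaller. It rests on assumed slopes of 0.15 to 0.30 for disability beyond baseline concern; it would be smaller if age and previous falls already carry that information. The chronic-conditions count was not simulated, so its separate contribution is not quantified.

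The protection against bias is conditional. Under strong arm-specific assumptions the bias is about 0.1 to 0.4 points, that is 0.1/3.8 ≈ 3% to 0.4/3.8 ≈ 11% of the target difference, and the change removes most of it. With equal health-related dropout there is none to remove. The documents do not support a claim that the trial's result will be biased.

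**What to change.** In the Analysis section, add the baseline GARS score and the chronic-conditions count to the fixed covariates of the effect models, and state that they are included whether or not the arms differ on them at baseline. Keep perceived general health, entered as a fair/poor indicator. Make the change before outcomes are examined by arm.

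Cost: one sentence and two degrees of freedom, against 389 participants. No new data and no change to sample size.

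### Covariates are added when baseline differences are detected, so the final covariate set of the primary models depends on chance imbalance and an undefined rule

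*Protocol article*

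**What the plan says.** The Analysis section of the protocol article sets out three steps.

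- A comparison of the arms: "Baseline variables will be compared, to detect differences between the participants of both groups at the start of the study".
- A fixed adjustment set, justified as relevant to the outcomes: "concerns about falls, age, gender, perceived general health, and number of falls in the past 6 months at baseline".
- An extension of that set: "Additional covariates will be included in the analysis if baseline differences are detected for variables relevant for the outcomes".

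The models concerned are the mixed-effects regressions used "to test for between-group differences with respect to the primary, secondary and tertiary outcome measures at all follow-up assessments". The extension is therefore part of the primary analysis, and nothing else in the article confines it to a sensitivity analysis. The article does not list the variables that could be added, say what counts as a detected difference, or cap the number of additions.

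The Randomisation section describes stratified allocation in blocks of two, with the level of concern about falls as the only stratification factor.

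**The concern.** If allocation was sound, a difference between the arms in an unstratified baseline variable is a chance event. It says nothing about whether adjusting for that variable will improve the estimate. What makes a covariate useful is that it predicts the outcome, whether or not it is balanced. The article follows this principle for its five fixed covariates and departs from it in the next sentence, where a relevant variable that happens to be balanced is left out.

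Two things are at stake. The first is precision: prognostic information is used only when the arms happen to differ. The second is prespecification: because relevance and detection are both undefined, two competent analysts could arrive at different final models for the same primary outcome.

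Baseline avoidance (FES-IAB) and disability (GARS) illustrate the first point. Both are measured at baseline according to Table 2, and neither is in the fixed set. Unless the mixed model carries the baseline value in another way, which the article does not settle, each would enter its own model only if it happened to be imbalanced.

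**Working it through.** **1. The plan's own design figure.** Inputs from Sample size and power: difference 3.8 FES-I points, SD 11.4, one-sided alpha 0.05, power 80%.

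n per arm = 2 × (1.645 + 0.842)² × (11.4/3.8)² = 2 × 6.18 × 9 ≈ 111.3, rounded up to 112.

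Power at 112 per arm is 80.2%. With 20% dropout, 112/0.8 = 140. Both stated figures reproduce, and the covariate rule does not enter either of them.

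**2. Chance that at least one extra covariate enters.** For k independent candidates, each judged at threshold a, the chance is 1 − (1 − a)^k. The article gives neither k nor a, so both are assumptions.

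| k | a = 0.05 | a = 0.10 |
|---|---|---|
| 5 | 23% | 41% |
| 10 | 40% | 65% |
| 15 | 54% | 79% |

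A loose upper figure comes from counting everything in Table 2: 12 scale scores at baseline plus 12 additional variables, 24 in all, less the five fixed covariates, leaves 19. Then 1 − 0.95^19 = 62% and 1 − 0.90^19 = 86%.

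**3. Effect on the test.** Simulation settings (all assumed unless sourced):

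- 156 per arm, from the 389 enrolled: 389 × 0.8 / 2 = 155.6.
- Ten independent candidates, each with correlation r with the outcome; together they explain 10r² of its variance.
- One-sided test at 5%; 8,000 null runs per row.
- For power, a true effect of 0.333 SD (3.8/11.4) and 3,000 runs per row.

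The strategies compared are covariates selected on imbalance, all candidates prespecified, and the better of the unadjusted and imbalance-adjusted results.

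| r | a | Error: selected | Error: all prespecified | Error: better of two | Power: selected | Power: all prespecified |
|---|---|---|---|---|---|---|
| 0.10 | 0.05 | 5.21% | 5.42% | 5.85% | 90.6% | 92.1% |
| 0.10 | 0.10 | 4.75% | 5.11% | 5.79% | 90.4% | 91.9% |
| 0.20 | 0.05 | 4.40% | 4.89% | 5.96% | 91.0% | 98.0% |
| 0.20 | 0.10 | 4.11% | 5.54% | 6.24% | 92.8% | 97.7% |
| 0.25 | 0.05 | 3.75% | 5.16% | 5.82% | 92.8% | 100.0% |
| 0.25 | 0.10 | 3.06% | 4.94% | 5.96% | 94.0% | 99.9% |

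The Monte Carlo standard error of a null entry is about √(0.05 × 0.95 / 8000) = 0.24 percentage points, so 5.21% cannot be told apart from 5%. With no extra covariates, power was 90–91% in these rows. Selection on imbalance therefore does not fall below an unadjusted analysis; it loses against prespecification.

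Five candidates at r = 0.3 gave the same pattern: error 3.6–4.3% with selection and about 5.6% for the better of two; power 91–92% with selection against 99% prespecified.

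**The case against.** The strongest defence is that the article already does most of what is asked. Five covariates enter whatever their balance, chosen because they matter for the outcomes. The extension has a relevance filter as well as an imbalance trigger, and a threshold or candidate list could sit in an analysis plan that is not shown. All of this is fair, and it limits the point to the added terms. It does not remove the point: the article states an imbalance-triggered rule for the main analysis, and a list or threshold defined elsewhere would not make imbalance a good criterion.

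A reader might draw four stronger conclusions that the document does not support.

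- That the primary model as a whole is picked by chance. Only additions to a fixed core are.
- That significance tests of baseline differences are prescribed. The article speaks of comparing and detecting, and names no test or p-value.
- That covariates are chosen after outcomes are seen. The trigger is baseline data, and the article does not say when the choice is made.
- That an altered covariate set is the likely result, on the strength of 62% or 86%. Those figures take all 19 variables as relevant, independent and formally tested. Several scales are plausibly related, such as the two HADS subscales; the TICS is given only to those who fail the AMT4; and the single-item concern question, if it is one of the 19, reflects the stratification factor.

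Comparing the arms may still serve as a check on the allocation process. That is a reason to describe them, not to select covariates from the comparison.

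**Conclusion.** The point holds in a limited form. The covariate set of the models, including those for the primary outcomes, is extended by a trigger that is the wrong criterion and is left undefined.

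It would be wrong to infer that the rule inflates the false-positive rate. Applied mechanically, it was nominal to conservative (about 3.1–5.2% one-sided), and more conservative as the candidates became more prognostic. The cost is power: about 90–94% against 92–100% with prespecification, still above the planned 80%. Error went above nominal, to about 5.8–6.2%, only where the better of two results could be reported. The loose wording leaves room for that, but nothing in the article says it is intended.

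These sizes rest on assumed thresholds, ten independent candidates and the assumed correlations. The upper end of the prespecified power range needs candidates that jointly explain 62.5% of the outcome variance (10 × 0.25²), which is generous. The statement that imbalances are due to chance rests on allocation having been sound.

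**What to change.** Delete the sentence that adds covariates on detected differences. Describe baseline characteristics by arm, and do not use that description to select covariates.

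Before outcome analysis, fix the set on prognostic grounds:

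- the stratification level of concern, age, gender, self-rated general health and falls over the preceding six months, for every outcome;
- in addition, the outcome's own baseline value wherever it is measured at baseline (FES-I, FES-IAB, GARS and the tertiary scales).

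The calendar-based fall outcomes have no baseline calendar value, because the Data collection section has the calendar issued after the baseline measurement. For these, the six-month fall history serves instead.

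Report any model with further covariates only as a labelled sensitivity analysis.

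The cost is wording; 112 and 140 per arm are unchanged. The one downside is that a chance imbalance in an unlisted variable is dealt with in the sensitivity analysis and not in the main model.
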